### Statistical analysis

Baseline characteristics of all randomized women will be compared descriptively between the study groups. Outcome comparisons will be made according to the treatment allocation at randomization on an ‘intention to treat’ basis. For the primary outcome, the difference in exacerbation rates between groups will be compared using a Poisson regression model. This will enable calculation of the incident rate ratio and associated 95% confidence interval.

For secondary outcomes, discrete outcomes (i.e. low birth weight) will be analysed using log binomial regression and continuous outcomes (i.e. birth weight, gestational age) analysed using linear regression. Continuous variables with repeated measurements (i.e. questionnaire results, ACQ score) will be analysed using a generalized linear mixed model (GLMM) with a random intercept for individuals to account for repeated measurements.

Planned sub-analyses will be undertaken to assess the effects of asthma control, FEV1, asthma medication use, cumulative ICS exposure, asthma knowledge and medication adherence, on the primary and secondary outcomes. SPSS Version 20 (SPSS Inc., Chicago, IL, USA). and Stata IC 11.1 (Stata, College Station, TX, USA) will be used for analyses. Statistical significance will be assessed at the 0.05 level using a two-sided comparative test.

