### Outcomes and measures

#### Primary study outcomes

The primary outcomes in this study will be the percentage of women that experienced exacerbations during pregnancy (moderate and severe) defined as events for which the participant sought medical attention (i.e. an unscheduled visit to a doctor, presentation to the emergency department room or admission to hospital, or when oral corticosteroids were used for treatment of asthma). Based on previous research undertaken by our research group it is hypothesised that participation in the Antenatal Asthma Management Service will result in a 20% reduction (absolute) in the incidence of asthma exacerbations during pregnancy in the intervention group compared to the control group [28].

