### Sample size

In recognition of potential differences in the implementation and successfulness of the intervention across two distinct treatment sites, the sample size was calculated to ensure adequate statistical power within each treatment site. The total sample size of 378 pregnant women at baseline (189 in each group and each treatment site) was determined by power calculations (using 90% power and a 5% level of significance) using the primary outcomes of difference in exacerbation rate between treatment groups. We considered a 20% decrease (absolute reduction from 45% to 25%) in the incidence of asthma exacerbations as both achievable and clinically significant. The calculated sample size includes an estimated 15% loss to follow-up. We estimate there are at least 360 pregnancies complicated by asthma each year at each hospital and we will need to recruit 27% (n = 95 per site each year) of women presenting to the antenatal clinic per year to complete study recruitment over 2 years.

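### The primary outcome and sample size concern the proportion of women with an exacerbation, but the stated analysis is a Poisson model giving an incidence rate ratio

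*Protocol article*

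**What the plan says.** Under Primary study outcomes, the outcome is "the percentage of women that experienced exacerbations during pregnancy (moderate and severe"), which is one yes/no per woman.

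The Sample size section plans on the same scale: "We considered a 20% decrease (absolute reduction from 45% to 25%) in the incidence of asthma exacerbations", "using 90% power and a 5% level of significance".

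The Statistical analysis section then says: "For the primary outcome, the difference in exacerbation rates between groups will be compared using a Poisson regression model", and adds: "This will enable calculation of the incident rate ratio and associated 95% confidence interval". It names no variance estimator and no absolute effect measure for the primary outcome. For the secondary outcomes, "discrete outcomes (i.e. low birth weight) will be analysed using log binomial regression".

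The Data collection section says that both the number and the timing of exacerbations will be determined, so the data would support either a yes/no or a count analysis.

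**The concern.** The outcome and the sample size are about how many women are affected. The model and its effect measure are those for how many events occur. The authors had a suitable model for yes/no data at hand, since they assign log-binomial regression to the other discrete outcomes, but named a different one for the primary comparison.

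Two things are at stake. First, the headline figure could be a ratio of women affected or a ratio of events, and neither is the 20-point absolute reduction on which the trial was planned. If that choice stays open until data are seen, the primary result is open to selection. Second, if the stated yes/no outcome is put into a Poisson model with default standard errors, the interval is wider and the test weaker than they should be.

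**Working it through.** **Inputs.** Proportions 0.45 and 0.25, 189 women per arm, 15% loss (Sample size); 5% loss (Abstract); two-sided 0.05 (Statistical analysis); prior-trial exacerbation rates 0.615 and 0.288 (Background, existing evidence on self-management education), assumed to be per pregnancy.

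**The plan's own sample size.** The usual two-proportion formula gives n per arm = [1.96·√(2·0.35·0.65) + 1.2816·√(0.45·0.55 + 0.25·0.75)]² / 0.20² = 117.4, so 118 per arm and 236 in total. Dividing by 0.85 gives 139 per arm (278); dividing by 0.95 gives 125 per arm (250). If each of two sites is to be fully powered, the totals are 472 without loss, 500 with 5% and 556 with 15%. None equals the stated 378. That is a separate matter; here the 45% and 25% show only that the trial was sized on proportions.

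**Reading 1: the model is fitted to the yes/no outcome with model-based variance.** Poisson takes the variance as p where the binomial variance is p(1 − p). With 15% loss, n = 189 × 0.85 = 160.65 per arm, and ln(0.25/0.45) = −0.588.

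- Poisson SE of the log risk ratio = √[1/(n·0.45) + 1/(n·0.25)] = 0.197.
- Correct SE = √[0.55/(n·0.45) + 0.75/(n·0.25)] = 0.162.
- Ratio = 1.214, whatever n is.
- 95% CI = exp(−0.588 ± 1.96·SE): 0.38–0.82 with the Poisson SE, 0.40–0.76 with the correct one.
- Power = Φ[(0.588 − 1.96·0.197)/0.162] = 0.894, against Φ[(0.588 − 1.96·0.162)/0.162] = 0.952.
- Under the null with common proportion p, the SE ratio is 1/√(1 − p). At p = 0.45 it is 1.348 and type I error is 0.8%; at p = 0.35 it is 1.240 and type I error is 1.5%.
- Real coverage of the nominal 95% interval is about 98.3%.

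Simulation (200,000 runs, 161 per arm) gave power of 91% with model-based and 97% with robust variance, and coverage of 98.4% and 95.2%. With 5% loss (179.55 per arm) the intervals are 0.39–0.80 and 0.41–0.75, and power is 93% and 97%.

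**Reading 2: the model is fitted to event counts.** The target becomes events per woman. The prior trial's rate ratio is 0.288/0.615 = 0.47; the planned risk ratio is 0.25/0.45 = 0.56. These are different quantities.

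Whether the interval is also wrong depends on overdispersion. For Poisson counts, the share of women with at least one event is 1 − exp(−0.615) = 45.9% and 1 − exp(−0.288) = 25.0%, close to the planned 45% and 25%. Negative binomial counts with mean 0.615 would give 1 − 1.3075⁻² = 41.5% at dispersion 0.5 and 1 − 1/1.615 = 38.1% at dispersion 1. Simulated coverage of the model-based interval at 161 per arm is 95.3% for Poisson counts, and 94.0%, 93.0% and 90.7% at assumed dispersions of 0.25, 0.5 and 1. Applying the severity-specific rates in the Background (13%, 26%, 52%) with assumed severity mixes gives a variance-to-mean ratio of about 1.13–1.18 and coverage of about 93%, before any adjustment for severity.

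**The case against.** The protocol uses the word rate loosely. The Background gives severity-specific exacerbation rates as percentages, and the Sample size section calls the 45% versus 25% contrast a difference in exacerbation rate. The analysis sentence can therefore be read as Poisson regression of the yes/no outcome. With robust variance, that is a valid risk-ratio analysis. Variance estimator, dispersion handling and offset are commonly left to an analysis plan, which is not shown, so silence on them is no fault. Even with model-based variance the error is conservative, and pooled power stays near the planned 90%.

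Much of this stands. A reader might infer that the plan specifies ordinary Poisson regression without robust variance, or that the interval is wrong however the outcome is coded. The document supports neither: it names no variance estimator, and the count interval fails only under overdispersion. A reader might also expect type I error of 8.7% to 12.3% under count coding. Those figures follow from assumed dispersions of 0.5 to 1.0 at a mean of 0.615, and the document's own rates and proportions sit close to Poisson. That closeness is not proof either, because the protocol does not say that the 45% was derived from the 0.615.

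What the objection does not remove is the conflict in the stated text. Outcome, planned effect, model and effect measure are all written down. An incidence rate ratio is not the planned contrast of proportions, and the protocol gives yes/no outcomes elsewhere a different model.

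**Conclusion.** The point holds as a mismatch: a proportion of women is defined and sized, and an incidence rate ratio from a Poisson model is reported.

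Under the yes/no reading, the 21% inflation of the standard error and its consequences are conditional on model-based variance, the planned proportions and, for the interval and power, 15% loss. They cost precision and power and do not produce false positives. Within one site (about 80 per arm) power would be about 57% instead of 73%; most of that shortfall from 90% comes from the sample size, not from the model.

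Under the count reading, the firm problem is that the analysis answers a different question. Too narrow an interval is a plausible risk that the document does not demonstrate.

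**What to change.** In the Statistical analysis section:

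- State that the primary analysis is of the proportion of women with at least one qualifying exacerbation after randomisation.
- Fit log-binomial regression, as for the other discrete outcomes, or Poisson regression with robust variance if it does not converge.
- Report the risk ratio and the absolute risk difference, each with a 95% confidence interval, so that the result can be set against the planned 20-point reduction.
- Make the number of exacerbations a secondary outcome, analysed by negative binomial or robust-variance Poisson regression with a time-at-risk offset.

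This changes wording only. The number and timing of exacerbations are already to be collected. The change should be made before the interim analysis planned after 189 women, so that the choice is fixed before outcome data are examined.

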### Cost effectiveness

A cost-effectiveness analysis will incorporate costs of providing standard care and the Antenatal Asthma Management Service, costs and quality of life effects associated with asthma-related adverse events, including mild and severe exacerbations, and fetal outcomes. This will determine whether, and under what circumstances, the provision of an Antenatal Asthma Management Service would be cost-effective. The economic evaluation will be performed from a societal and health care perspective. Direct medical costs (i.e. costs of intervention, asthma related consultations) as well as indirect costs (i.e. asthma related quality of life) will be taken into account. Relevant fixed unit costs associated with the delivery of standard care and the Antenatal Asthma Management Service intervention (i.e. costs of running the antenatal clinic, visits with respiratory nurse and respiratory specialist/preferred GP) will be estimated and allocated proportionally across the patients in the respective trial arms.

Additional costs associated with respiratory related health-care (i.e. asthma exacerbations, medication treatment costs), antenatal related health-care (i.e. pregnancy complications, medication treatment costs) and neonatal related health-care (i.e. admission to NICU) will be identified to determine a total cost estimate for the mother and child. We will obtain consent from patients to access all Medicare Benefits Schedule (MBS) (i.e. GP consultations) and Pharmaceutical Benefits Schedule (PBS) (i.e. medication costs) data to collate accurate data on unit costs associated with receiving either intervention during pregnancy. We will also obtain consent to access public hospital data, and so will capture emergency, outpatient, and inpatient encounters and the relevant unit costs associated with these encounters.

Missing cost data, for example, from patients who did not consent to access to their MBS, PBS, and public hospital data will be imputed using the Multiple Imputation using Chained Equations (MICE) approach.

To analyse long-term cost-effectiveness, extrapolation models for adverse neonatal outcomes (e.g. low birth weight and IUGR) will be developed, based on existing literature. A structured review of the literature will inform the costs and consequences (i.e. effects on Quality of Life) of adverse neonatal outcomes identified, which will be synthesised to model the short- and longer-term additional health-related events that a cohort of such babies would be expected to experience over their lifetime, or over a defined time horizon (e.g. 20 years). Similar lifetime extrapolation models have previously been developed in the areas of thalassaemia and sickle cell disease [40,41]. The resulting dataset will contain estimates of the short- and long-term costs and outcomes for all patients (mother and child), and will be analysed to estimate the expected costs and outcomes in the patient cohorts receiving the different levels of care.

To facilitate cost-effectiveness comparisons with interventions across other disease areas, outcomes for both mothers and children will be converted to quality adjusted life years (QALYs). Utility weights for mothers will be derived from responses to the AQoL [42], for which an Australian-based algorithm is available. The extrapolation models for fetal outcomes will incorporate literature-based health state utility weights for events included in the model to estimate QALYs gains in this population. The within trial analysis will report the costs and varied consequences (i.e. effects on mother and baby) of the different interventions. To inform comparisons with the cost-effectiveness of interventions across the health care system, the data from the study will be combined with the extrapolation models to estimate the expected incremental cost per QALY gained as a result of the Antenatal Asthma Management Service.

Every trial participant will have an estimated lifetime cost, and QALY value. If imbalances in baseline characteristics across the treatment groups are observed, propensity weighted generalized linear models will be used to generate adjusted mean cost and QALY estimates for each treatment group. In the absence of imbalance, the mean cost and QALY estimates in each group will inform mean incremental cost-effectiveness ratios, and incremental net monetary benefits.

Uncertainty will be represented using deterministic and probabilistic (bootstrapped) sensitivity analyses. The probabilistic analysis will inform credible intervals around the incremental cost-effectiveness ratios and cost-effectiveness acceptability curves based on alternative assumed monetary equivalent values of a QALY.

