### Setting

This study will involve two public hospital antenatal clinics which account for 40% of all births in South Australia, Australia. These hospitals are the Lyell McEwin Hospital (LMH) and Flinders Medical Centre (FMC). A clinical study has been running at the LMH throughout 2012 to demonstrate the feasibility of implementing an Antenatal Asthma Management Service. During this period approximately 40 referrals have been received each month from the antenatal outpatient clinic for women with asthma. This represents an estimated prevalence of asthma in this population of 14%. This high prevalence is likely due to the fact that more than 70% of women with asthma use public health care and that the prevalence of asthma is higher among those with lower socioeconomic status [14], reflective of the area in which LMH is situated. In comparison to the LMH, FMC is situated in a region of higher SES than LMH (SA Health Atlas). This will enable the clinical and cost-effectiveness of the service to be investigated in two diverse settings, as previous research has identified that SES is a significant risk factor for outcomes related to maternal asthma [30].

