### Treatment schedules

#### Standard care group

Standard care will be as outlined in the SA Perinatal Practice Guideline for the treatment of asthma during pregnancy (Available from http://www.sahealth.sa.gov.au). This involves women with asthma self managing their disease during pregnancy and seeking guidance for asthma management when required from a midwife, obstetrician, respiratory physician or GP. Some women in this group will already be managed by a respiratory specialist and this will be continued. While women receiving standard care will be followed-up at exactly the same time points as those in the intervention group, no formal attentional control will be utilized. Notably, while some researchers advocate for the use of attention controls there is, at this point in time, a significant lack of understanding regarding what constitutes an appropriate attention control group. There is also a lack of understanding regarding the potential benefits (or biases) associated with the use of an attention control, limiting its ability to be utilized in this setting [39].

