#### Intervention group

The intervention group will receive care through the nurse-led Antenatal Asthma Management Service, based in the antenatal outpatient clinic. The Antenatal Asthma Management Service will be led by a respiratory nurse with qualifications in asthma management and education and spirometry. The details of the methodology to be used for nurse-led respiratory care in our study have been previously published [17]. All asthmatic women will receive asthma education with a full assessment of their asthma at 18, 24, 30 and 36 weeks gestation conducted by a respiratory nurse. Each antenatal visit will include a 60 min session where asthma management skills are assessed including: medication adherence and knowledge, inhaler device technique, recognition of asthma deterioration and possession of a written asthma action plan [17]. In addition, subjects will receive education about asthma control and management skills including trigger avoidance and smoking cessation counseling when appropriate [17]. While it is standard antenatal care for all pregnant women to complete a smoking questionnaire at their first booking visit and be encouraged to quit smoking, an additional key component of the Antenatal Asthma Management Service will be in providing additional counseling on the importance of smoking cessation in relation to their asthma and the health of their baby. Women will be provided with information on the benefits of smoking cessation and direct referrals will be made to QuitSA for cessation support.

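### Truly fixed service costs are spread over trial-arm patients, so the cost per woman reflects recruitment rather than routine throughput, and no throughput scenario is named

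*Protocol article*

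**What the plan says.** The Cost effectiveness section covers fixed unit costs of delivering standard care and the service. It gives as examples "i.e. costs of running the antenatal clinic, visits with respiratory nurse and respiratory specialist/preferred GP", and says that these costs "will be estimated and allocated proportionally across the patients in the respective trial arms". The resulting costs feed the incremental cost-effectiveness ratio, the net monetary benefit and a cost per QALY meant for comparison across the health system. Uncertainty is to be handled by deterministic analyses and a bootstrap. Throughput is not mentioned, and no step rescales fixed costs to the volume of a routine service.

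The volumes come from other sections. Setting: "This study will involve two public hospital antenatal clinics". Sample size: "The total sample size of 378 pregnant women at baseline (189 in each group and each treatment site"), a plan to "recruit 27% (n = 95 per site each year) of women presenting to the antenatal clinic per year to complete study recruitment over 2 years", and "We estimate there are at least 360 pregnancies complicated by asthma each year at each hospital". The Intervention group section schedules assessments at 18, 24, 30 and 36 weeks and adds: "Each antenatal visit will include a 60 min session where asthma management skills are assessed".

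**The concern.** Cost effectiveness is half of the single stated aim, and the Discussion offers the results as a basis for policy and service models. The economic question is therefore about routine provision. A fixed cost per woman depends on how many women share it. If the sharing group is the intervention arm, its size follows from the recruitment target and the allocation ratio, neither of which tells a hospital what the service would cost to run.

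Some inputs that the article describes need not grow with the number of women seen: clinic running costs, an on-call respiratory physician (Intervention group) and six-monthly physician quality review at each site (Trial management). Dividing such items by a small trial arm makes the service look dearer than it would be at a higher volume. That raises the incremental cost and could turn an adoption decision against the service.

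**Working it through.** **Inputs from the Sample size section.** Total 378; two sites; two years; equal groups of 189; 95 recruits per site per year; at least 360 asthma pregnancies per hospital per year.

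**Reproducing the plan's figure.** 378 / 2 sites / 2 years = 94.5, which matches the stated 95. As a share of 360, 95/360 = 26.4%, against the stated 27% (0.27 × 360 = 97). The figures agree to within rounding.

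**Women in the service during the trial.** With 1:1 allocation, 95/2 = 47.5 per site per year (47.25 from the unrounded 94.5).

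**Fixed component.** Overstatement = V / 47.5, where V is the routine yearly volume per site.
- V = 360 (full uptake): 360/47.5 = 7.58
- V = 180 (50%): 180/47.5 = 3.79
- V = 97 (27%): 97.2/47.5 = 2.05

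The 360 is a count of asthma pregnancies, not a service volume. The Setting section reports about 40 referrals a month in the feasibility study at one site, or 40 × 12 = 480 a year, so a volume of that order is plausible but not documented.

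**Volume-driven component.** Four 60-minute sessions are 4 nurse-hours per woman. That is 47.5 × 4 = 190 hours per site-year in the trial and 360 × 4 = 1,440 hours at full uptake. Total hours rise with volume, but hours per woman do not change, so this part of the cost is not overstated.

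**Total service cost per woman.** Let f be the share of trial-volume cost that is truly fixed. The document does not give f, so the values below are assumptions. Overstatement = 1 / (1 − f + f × 47.5/V).

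| V per site-year | f = 10% | 20% | 50% | 70% | 80% | 100% |
|---|---|---|---|---|---|---|
| 360 | 1.10 | 1.21 | 1.77 | 2.55 | 3.27 | 7.58 |
| 180 | 1.08 | 1.17 | 1.58 | 2.06 | 2.43 | 3.79 |
| 97 | 1.05 | 1.11 | 1.34 | 1.56 | 1.69 | 2.05 |

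Setting the formula equal to k gives the fixed share needed for a k-fold overstatement: f = (1 − 1/k) / (1 − 47.5/V). At V = 360, a two-fold error needs f = 0.5/0.868 = 58%, and a three-fold error needs f = 0.667/0.868 = 77%.

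The base of the share matters. If g is the fixed share of the full-volume unit cost, the ratio is (1 − g) + 7.58g. At g = 25% this is 2.64, but that corresponds to 1.895/2.645 = 72% of the trial-volume cost. Any assumed share should say which base it uses.

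**Does the planned uncertainty analysis show it?** A fixed cost spread evenly over an arm is the same constant for every woman in it. Resampling women returns that constant unchanged, so bootstrap intervals and acceptability curves would describe precision around a shifted mean. A deterministic analysis could show the shift, but only if throughput is one of the quantities varied.

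**The case against.** The strongest reply is that the sentence need not mean a division of overhead by trial patients alone. It speaks of unit costs, and its examples mix clinic overhead with visits, which carry a price per use. Proportional allocation could mean unit prices applied by use, or the trial arms' share of a clinic that already serves many others. Under either reading there is little or no overstatement. This stands as a limit on certainty. It does not remove the point, because the plain reading is a stated rule with trial-arm patients as the base, and the readings give different costs.

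Second, costing at trial volume is a recognisable choice for a within-trial analysis, and an article may leave named scenarios to a fuller economic plan. This also stands in part. It is a reason to keep the trial-volume result and add to it, not to replace it.

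Three stronger readings are tempting, and the document supports none of them.
- A reader might infer that the total cost per woman is overstated several-fold. That needs most of the cost to be fixed and uptake to be high. The service as described consists largely of hour-long nurse visits, and no fixed share is given.
- A reader might infer that the service would see 360 women per site. The article gives that figure in a sentence on recruitment feasibility; some of these women would be in remission or would decline.
- A reader might infer that control-arm research visits inflate the comparator, since "women receiving standard care will be followed-up at exactly the same time points as those in the intervention group". The cost list names no research-midwife visits, standard care is described as self-management with advice when needed, and the baseline assessment is common to both arms. Nothing shows that these visits would be costed.

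**Conclusion.** The point holds for truly fixed costs, on the plain reading of the allocation sentence. The direction is clear: the service looks dearer than it would at any routine volume above about 47 women per site per year. The fixed component could be overstated about 7.6-fold at 360 a year, 3.8-fold at 180 and 2-fold at 97. The total service cost per woman at 360 a year would be about 1.1 to 1.8 times too high if 10% to 50% of trial-volume cost is fixed.

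These sizes rest on two assumptions that the document does not settle, the fixed share and routine uptake, so they are a range and not an estimate of error. The effect on the cost per QALY cannot be computed from what is given. This is a cheap improvement to a stated rule, not a flaw that invalidates the economic evaluation.

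**What to change.** In the Cost effectiveness section:

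1. Cost nurse visits by the contact time used (the 60-minute sessions plus reporting time), and keep them apart from costs that do not vary with volume.
2. List the truly fixed and set-up costs, and state the base over which they are allocated.
3. Beside the trial-volume allocation, report a named deterministic scenario that spreads the fixed costs over routine throughput, for example 27% to 100% of 360 women per site per year (about 97 to 360).

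The cost is a wording change and one extra scenario in the economic model, with no change to randomization, visits or outcomes. The downside is that routine throughput and the fixed share have to be assumed, so both should be shown as ranges. Which allocation serves as the base case is open to debate; reporting both lets the reader see how far the conclusion depends on volume.
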